## Abstract

**Background:**

Major depressive disorder (MDD) is a highly prevalent (8–15%), severely disabling disorder and is associated with enormous socioeconomic impact. Antidepressant medication for the treatment of MDD has proven effective in RCTs; however, placebo response is also substantial. Given the potential benefits of modulating the placebo response in patient care and pharmacological research, understanding the mechanisms underlying placebo response is of high clinical relevance. The placebo response is mediated by treatment expectation, i.e. an individual’s belief about whether and how much they will improve as a consequence of their treatment. The mechanisms and moderators of treatment expectation effects in MDD are poorly understood. Initial brain imaging studies on placebo responses in MDD point towards the relevance of the lateral prefrontal cortex and the rostral anterior cingulate cortex (rACC). In this project, we will investigate the neural mechanisms underlying the antidepressant effects of treatment expectation associated with the fast-acting antidepressant esketamine in patients with MDD. Esketamine is an NMDA receptor antagonist inducing antidepressant effects within hours.

**Methods:**

We will employ a fully balanced placebo design with the factors “treatment” (i.v. esketamine / placebo) and verbally induced “expectation” (high / low) combined with fMRI (resting state, emotion and reward processing paradigms) to investigate the psychological and neural mechanisms underlying the antidepressant effects of expectation, and how these interact with the pharmacological effects of esketamine.

**Discussion:**

The insights gained by this project promise fundamental implications for clinical treatment and future drug trials. Unraveling the mechanisms underlying expectation effects on antidepressant treatment may inform (1) strategies to modulate these effects and thus improve assay sensitivity in RCTs and (2) novel treatment regiments aiming to maximize the synergistic effects of expectation and pharmacological treatment in the clinical care of patients with MDD.

**Trial registration:**

This trial has been prospectively registered with the EU Clinical Trials Register: EudraCT-No.: 2020–000784-23 (November 17, 2020).

## Introduction

### Background and rationale {6a}

Major depressive disorder (MDD) has a lifetime prevalence of around 8–15%, affecting about 300 million people worldwide. MDD is the leading global cause of disability in terms of total years lost due to disability and is associated with excess mortality [1]. About one third of patients with MDD fail to achieve remission despite treatment with multiple antidepressants and are considered to have treatment-resistant depression [2]. Treatment algorithms suggest that an antidepressant medication be started initially at lower doses and that adjustment of the medication maybe considered if at least a moderate improvement is not observed after 4–6 weeks. This means that even in patients who do respond to antidepressants the time to onset of effect can be several weeks. During this time, patients may remain symptomatic and at risk of suicidal behaviour. An unresolved issue in antidepressant trials are high placebo responses which has been suspected to contribute to so-called failed antidepressant trials [3]. Patients’ expectation about treatment benefits is thought to play a major role in the placebo response [4]. The neural circuits involved in the effects of treatment expectation on pain and affective processing include limbic and reward-related brain areas (e.g. amygdala, rostral anterior cingulate cortex striatum) as well as the prefrontal cortex [5, 6]. Knowledge of the differential neurobiological mechanisms underlying the response to pharmacological treatments vs the effects of positive expectation in MDD is almost completely lacking. Better knowledge of such mechanisms would significantly improve our understanding of antidepressant effects and ultimately help us to provide more effective relief of depressive symptoms for patients.

#### Functional neuroimaging of emotion and reward processing in MDD

Most patients with MDD present with low mood and anhedonia (i.e. loss of pleasure and blunted responsiveness to reward). The severity of these cardinal symptoms of MDD is related to emotion dysregulation (low mood) and deficits in reward value processing (anhedonia) [7]. Structural and functional magnetic resonance imaging (MRI) studies in MDD (irrespective of treatment) vs healthy subjects have identified distinctive morphological and functional brain changes in MDD mainly in cortico-limbic networks [8, 9]. Brain regions involved in these networks, in particular DLPFC, insula, rACC, and amygdala, are crucial for the processing of information with emotional (e.g. emotional faces) or motivational (e.g. monetary rewards) significance. Functional imaging data acquired while patients with MDD process emotional stimuli have widely demonstrated altered physiological responses in the amygdala as well as in anatomically related areas [10], with negative emotional stimuli (e.g. fearful faces) eliciting enhanced amygdala responses in patients [8], while amygdala hypo-activity has been found in relation to positive facial expressions [8, 9]. The brain reward system (BRS) mediates reward behaviours, pleasure, and motivation and has been associated with anhedonia [11]. A number of fMRI studies have been conducted in order to elucidate brain reward processes involved in MDD [11, 12]. For example, using a monetary incentive delay task in adults with or without MDD, one study found relatively reduced putamen activation during reward anticipation, reduced activation in nucleus accumbens (Nacc) and caudate during receipt of reward [13] and increased ACC activation during anticipation of monetary gains in the MDD group [14]. It is yet unclear how alterations in the emotional and reward systems are related to treatment expectation in MDD.

#### Neural-functional targets of antidepressant treatment and placebo in MDD

Functional MRI studies have helped to identify brain regions responding to antidepressant treatments in healthy people and patients with MDD. Generally, these regions are part of emotion- and reward-processing networks, i.e. DLPFC, insula, ACC and amygdala [15]. More specifically, antidepressant treatment (mainly SSRI and SNRI) has been found to normalize abnormally elevated responses to mainly negative emotional stimuli particularly in the amygdala but also other limbic areas (e.g. ACC), to enhance PFC activity and to enhance the coupling between subcortical (amygdala, thalamus, striatum) and cortical (ACC, PFC) regions in patients with MDD (see [15] for a review). Yet, it is unclear how drug-specific effects separate from other non-specific elements of the treatment response, such as the placebo effect [16]. This is important, as placebo response rates in antidepressant clinical trials average 35–40% compared with response rates to antidepressants of around 50% and there is some evidence that the placebo response rate increases with increasing publication year [3], although this is subject to debate [3].

While pioneering studies have started to reveal the neural basis of placebo effects in emotional processing in healthy volunteers (see [17] for a review), the mechanisms underlying the antidepressant effects of expectation induced by placebo treatments in MDD are largely unexplored. Studies of the neural mechanisms underlying placebo effects in antidepressant treatment have largely been limited to demonstrating differences in brain activity between responders and non-responders to placebo. The few available studies on placebo responses in MDD point towards a contribution of the PFC and rACC [6, 18, 19]; however, their naturalistic design cannot support identification of the mechanisms underlying placebo effects, such as patient outcome expectation [20]. To date, only one few randomized controlled studies designed to identify the neural mechanisms of expectation augmentation in antidepressant treatment have been published. An SSRI randomized control trial has been published. The results of the first study [21] suggested that manipulating outcome expectation through increasing the probability of receiving active medication (SSRI vs placebo) was associated with decreased amygdala activation in response to sad emotional faces, which in turn was associated with more rapid reduction in depressive symptoms during the course of later antidepressant treatment. However, the sample size of this study was small (total *N* = 23 patients, only 4 patients randomized to placebo condition). A larger study (*N* = 66) using a similar design aimed to identify baseline neuroimaging and cognitive predictors of response to expectancy effects in elderly outpatients with MDD [22]. Patients benefiting from the manipulation in terms of greater antidepressant treatment response showed greater processing speed, executive function and frontostriatal white matter tract integrity. Antidepressant medication was, however, heterogeneous in this trial and the designs of both studies did not allow to differentiate between expectation related antidepressant effects and unspecific effects (e.g. natural history, additional psychological therapies) due to the delay between expectation induction and actual antidepressant or placebo treatment. In order to develop novel treatment strategies for patients which provide effective symptom relief it is crucial to understand expectation mechanisms early in the treatment process, ideally after a single-dose of a fast-acting antidepressant, which may help to identify responders to antidepressant or placebo treatment early, with the benefit of avoiding unnecessary dose increases and side effects. Based on these considerations, we will use esketamine as a fast-acting compound in a large sample of MDD patients (*N* = 176) which will allow us to perform the expectation manipulation and the measurement of its effects on the same day.

#### Fast-acting antidepressant esketamine: clinical utility and pharmacological MRI

Besides serotonergic, noradrenergic (emotion processing) and dopaminergic (reward processing) systems, abnormalities in glutamatergic neurotransmission have been implicated in the pathophysiology of MDD. Importantly, the N-methyl-D-aspartate (NMDA) receptor antagonist ketamine—which has been in use as an anaesthetic for decades—has antidepressant effects in subanaesthetic doses within hours. This rapid effect distinguishes it from conventional compounds which induce a clinically relevant effect only after 1–3 weeks. A recent meta-analysis of randomized, placebo/pseudo-placebo-controlled trials of single-dose, i.v. ketamine or non-ketamine NMDAR antagonists for treatment-resistant patients with MDD and bipolar depression has shown that single ketamine infusion was significantly superior to placebo/ pseudo-placebo regarding antidepressant efficacy [23]. The significantly greater reduction in depressive symptoms started within 40–60 min, peaked on day 1 and lasted until days 5–8, with maintenance of superior remission and response status until days 3–5 and 7, respectively. Effect sizes ranged from small to large (− 0.38 to − 1.00) for symptom reduction (large for response [NNT = 2–5, peaking at 230–240 min] and remission [NNT = 3–7, peaking at 1 day]).

Recently, a novel route of administration has also been introduced. Esketamine, the S-enantiomer of ketamine with a higher affinity for the NMDA receptor than the R-enantiomer, can be applied as a nasal spray. Following intranasal application of esketamine, robust and durable antidepressant efficacy has been demonstrated in treatment-resistant MDD [24]. The neural signaling changes induced by administration of sub-anaesthetic esketamine can be measured using pharmacological magnetic resonance imaging (phMRI). The existing studies in patients with MDD have used ketamine i.v.; no phMRI study using esketamine in patients with MDD has been published so far. PhMRI studies aiming to identify the neural correlates of ketamine treatment by use of (resting state) fMRI, diffusion tensor imaging (DTI), magnetic resonance spectroscopy (MRS) and magnetoencephalography (MEG) show that ketamine produces robust and consistent effects throughout the entire brain (see [25] for a review). A few phMRI studies using various methods (MEG, rsfMRI, fMRI, DTI, MEG, MRS) have focused on ketamine effects on brain networks relevant for emotion processing and suggest that ketamine alters activity in and increases functional connectivity between regions such as the right lateral PFC, sgACC, bilateral amygdala, NAcc, hippocampus and thalamus [26–29], with ketamine-induced changes correlating with the antidepressant effect. Only a limited number of studies have specifically focused on investigating ketamine’s impact on brain regions responsible for reward processing. One study has used fMRI to investigate the effects of ketamine i.v. (without placebo) on the functioning of neural networks specifically related to reward processing in 10 patients with treatment-resistant MDD [30]. This study found that mood improvement was accompanied by an increased recruitment of the orbitofrontal cortex, ventral striatum, medial substantial nigra and ventral tegmental area, structures that are part of the reward system. Using an ROI-based approach, a second study found a significant drug effect particularly in the nucleus accumbens and putamen in 37 unmedicated remitted patients with MDD during a Monetary Incentive Delay Task (MID; [31, 32]). Additional evidence for ketamine’s modulatory effects on brain regions involved in reward processing was provided by a study showing that ketamine reduced sgACC hyper-activation to positive incentives in 28 patients with MDD, indicating a normalizing effect of ketamine on aberrant sgACC functioning [33].

The existing fMRI studies on ketamine mechanisms in MDD generally have (i) small sample sizes, (ii) usually no placebo condition, (iii) only included treatment-resistant patients, (iv) not used esketamine in MDD, (v) only used i.v. administration and, most importantly, (v) did not investigate expectation effects which are very likely to contribute to the success of a novel treatment approach such as esketamine. Taken together, the rapid antidepressant effect and its robust effects on brain regions critically relevant for the pathophysiology of MDD make application of esketamine vs placebo an ideal model to disentangle treatment and treatment expectation effects at the neural and the behavioural level in MDD.

### Objectives {7}

The aim of this study is to provide evidence for the effects of positive expectation (high/low) on the neural and behavioural correlates of response to antidepressant treatment in patients with MDD. We will manipulate outcome expectation by disclosing different probability rates (high probability = 90%, low probability = 10%) of receiving a fast-acting antidepressant (i.v. esketamine) vs placebo in this randomized controlled trial. Using functional and structural MRI techniques, we will assess the effects of expectation manipulation, pharmacological treatment and the interaction thereof on the neural processes related to core MDD features, namely emotional dysregulation (Study 1: Emotion processing) and anhedonia (Study 2: Reward processing). The study will be performed as part of the Collaborative Research Center (CRC) SFB / TRR 289 “Treatment expectation”. This CRC aims to investigate the role of patients’ expectations about treatment benefits as important modulators of health outcomes. The ultimate goal of the CRC is to generate the knowledge base for the systematic utilization of patients’ expectations in order to optimize therapeutic strategies and thereby improve health outcomes. In a highly interdisciplinary and translational effort, the CRC will investigate the psychological and neurobiological mechanisms of as well as the interindividual differences in the effects of expectation on health outcomes. The present study will therefore also provide standardized behavioural, (f)MRI data for pooled and meta-analytic approaches within the CRC to identify predictors of interindividual differences in the effects of expectation on health outcomes.

### Trial design {8}

A double-blind, randomized, controlled parallel-group, 4-arm, monocentre trial using a balanced placebo design in a pharmacological fMRI study and exploratory framework.

## Methods: participants, interventions and outcomes

### Study setting {9}

A total of 176 patients with MDD according to DSM-5 criteria will be recruited from in- and outpatient settings from the Department of Psychiatry and Department of Psychology, University of Marburg, the Department of Clinical Psychology, University of Marburg and surrounding psychiatric hospitals. The diagnosis will be confirmed by a specialized psychiatrist or psychologist using the Structured Clinical Interview for DSM-5 (SCID-5). All patients will visit the lab 6 times (see Fig. 1 and Table 1, first and last 2 visits possible as telephone interviews in outpatients) and will be financially compensated for participation. All participants will have to be on a stable antidepressant medication for at least 2 weeks.

**Fig. 1 Fig1:**
[figure not shown]
Study design. One hundred seventy-six patients with acute MDD will be recruited (d-3), undergo baseline assessment (d0_1_), female participants of child bearing age will undergo a serum pregnancy test (d-3). At d1, patients will be randomized into 4 groups with the factors treatment (esketamine/placebo) and expectation (high/low). They will take part in two fMRI studies, rsfMRI, DTI and T1 scanning. Clinical outcomes will be assessed after 2 h, 4 h (all d1), 24 h (d2), 3d and 7d post treatment. Urine pregnancy tests will be performed at day 28

**Table 1 Tab1:**
[figure not shown]
SPIRIT participant timeline fort he EXPECT study

^a^BDI-II and GASE only

### Eligibility criteria {10}

#### Inclusion criteria

A current depressive episode lasting at least four weeksAn initial score of at least 7 (corresponding to a mild degree of depression) on the Montgomery Åsberg Depression Rating Scale (MADRS)Negative serum pregnancy test in women of childbearing potentialPatients with reproductive potential must agree to maintain highly effective methods of contraception by practicing abstinence or by using at least two methods of birth control from the date of consent through the end of the study. If abstinence could not be practiced, a combination of hormonal contraceptive (oral, injectable or implants) and a barrier method (condom, diaphragm with a vaginal spermicidal agent) has to be used.

#### Exclusion criteria

Psychotic symptoms (ascertained using SCID-5 Interview)Suicidality (clinical assessment by study physician)Hypertension > 180/100 mmHg (according to resting blood pressure, as assessed by study physician using blood pressure measurement)Hyperthyroidism (clinical history by study physician and current thyroid parameters will have to be within the following ranges: TSH 0.34–5.6 mU/l, fT3 3.2–6.9 pmol/l, fT4 7.5–21 pmol/l)Hepatic dysfunction (clinical history by study physician and current liver parameters will have to be within the following ranges: GOT < 35 U/l; GPT < 35 U/l; GGT < 40 U/l, bilirubin 0.1–1.2 mg/dl)Hypersensitivity to the active substance of esketamine or to any of the excipients listed in Sect. 6.1 of the SmPC (clinical history by study physician)Unstable angina or myocardial infarction in the last 6 months (clinical history by study physician)Myocardial failure (clinical history and physical examination by study physician)Glaucoma or perforating eye injuries (clinical history by study physician) Patients will be excluded if they have any drug or alcohol dependency/abuse within the previous 3 months or if they are under acute influence of alcohol (clinical assessment by study physician and alcohol breath test) Any contraindications for MRI, i.e. non-removable medical devices (such as pacemakers, insulin pumps, implantable drug infusion pumps) or metal devices /foreign bodies (such as aneurysm clips, metal splinters in the eye, intrauterine devices) and pregnancy (clinical assessment by study physician and serum pregnancy test) Medical conditions likely to affect brain anatomy or physiology (clinical assessment by study physician) Age < 18 or > 65 years Inability to provide written informed consent Breastfeeding (clinical history by study physician) Simultaneous participation in other clinical trials if not permitted by the Principal Investigator Patients for whom an elevated blood pressure or an increased intracranial pressure represents a serious risk will be excluded (clinical history and blood pressure measurement by study physician) Patients with manifest ischemic heart diseases will be excluded (clinical history by study physician) Increased intracranial pressure (clinical history by study physician) Severe psychological disorders other than depression (Structured Clinical Interview for DSM-5 (SCID-5)) Concomitant therapy with Xanthin-derivates and ergometrin (clinical history by study physician) Treatment with strong inhibitors or inducers of CYP3A4 (for example, but not exclusively, HIV protease inhibitors, macrolide antibiotics, azole antifungals, carbamazepine, phenobarbital (clinical history by study physician)) Benzodiazepine treatment (clinical history by study physician)

### Who will take informed consent? {26a}

Study physicians will inform the patients and obtain the consent for the trial.

### Additional consent provisions for collection and use of participant data and biological specimens {26b}

Not applicable as this trial does not involve collecting biological specimens for storage.

## Interventions

### Explanation for the choice of comparators {6b}

Antidepressant medication for the treatment of MDD has proven effective in RCTs; however, placebo response is also substantial. Given the potential benefits of modulating the placebo response in patient care and pharmacological research, understanding the mechanisms underlying placebo response is of high clinical relevance. The placebo response is mediated by treatment expectation, i.e. an individual’s belief about whether and how much they will improve as a consequence of their treatment. The mechanisms and moderators of such treatment expectation effects in MDD are poorly understood and will be investigated in this study. To this end, placebo (sodium chloride 0.9%) will be used as a comparator.

### Intervention description {11a}

#### Study 1: Emotion processing

The first fMRI study aims to characterize the effects of positive expectation (high vs low) and esketamine (verum vs placebo) on neural circuits underlying emotion processing in patients with MDD. To this end, the patients will perform an implicit emotion processing task involving positively and negatively valenced stimuli (happy and fearful faces) and indicate the gender of the person displayed by button press (for details, see “fMRI paradigms” below and Fig. 1) after having received the expectation induction followed by the study medication. Measures of treatment expectation, depression symptoms and treatment related side-effects will be assessed after baseline instructions and at 7 timepoints from 40 min to 1 week after treatment. Further information on methodological details are provided below.

#### Hypotheses

The (main) effect of positive expectation (high/low) on emotional (face) processing will be associated with increased PFC and amygdala activity.We expect an additive main effect of expectation and medication at the behavioural and neural level, such that effects are most pronounced in the high expectation + verum group and lowest in the low expectation + placebo group (high + verum > low + verum ≥ high + placebo > low + placebo).Baseline activation in regions involved in emotion processing (in particular VMPFC, amygdala) will be predictive of 4-h and 1-week treatment effects.Baseline VMPFC and rACC functional (rsfMRI) and structural (DTI) connectivity with amygdala predicts placebo treatment response after 4 h [24].The impact of positive treatment expectation (high/low) on symptoms of depression will differ between subjective and objective outcome measures of depression (MADRS vs BDI).

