#### Hypotheses

Positive treatment expectation (high/low) in MDD will result in enhanced VMPFC activation during reward processing.Baseline activation in regions of the mesolimbic system during reward processing (in particular hippocampus, NAc) will be predictive of 4-h and 1-week treatment effects.High vs low treatment expectations in MDD will differentially affect VMPFC activation during reward processing.More specifically, we expect that the interaction of treatment expectation and treatment indicates most pronounced effects in the high expectation + verum group and lowest in the low expectation + placebo group (high + verum > low + verum ≥ high + placebo > low + placebo).Baseline VMPFC and rACC functional (rsfMRI) and structural (DTI) connectivity with hippocampus predicts placebo treatment response after 4 h [24].

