##### Factor 2 Expectation (high/low)

While all patients will be correctly and non-deceptively informed that they are going to be randomized to placebo or verum, treatment expectation will be varied by providing incorrect probabilities for this randomization. In the high expectation group, participants will be (deceptively) informed that the study medication most likely (90%) contains the active drug, while the low expectation group will be (deceptively) informed that it is very unlikely (10%) that the study medication contains the active drug, but placebo [34]. One hour after expectation induction and receiving the study medication, patients will undergo MRI measurements: T1, DTI, fMRI resting state and two experimental “fMRI paradigms” addressing emotional and reward processing: (1) implicit processing (gender judgement) of positive and negative emotional faces (emotion processing) and (2) reward processing [31]. The paradigms are chosen because they (i) investigate emotional-cognitive-behavioural processes relevant for expectation formation and they reliably activate brain networks implicated in (ii) MDD, (iii) its treatment effects and (iv) placebo response in previous studies. Psychometric assessments at baseline will include BDI, MADRS, YMRS, expectation scale, dissociative experience scale and GASE. After pharmacological challenge assessments will include BDI, MADRS, YMRS, dissociative experience scale, GASE at 40 min, 4 h, 24 h, 3 days (+ expectation scale) and 7 days (+ expectation scale) after treatment (cf. “Data collection and management” section; adapted versions for symptom assessment at present will be used for assessments from 40 min to 3 days post-dose.) Treatment outcome in response to expectation and drug treatment will be assessed at the behavioural, subjective and neural level. After the end of the study (day 7 after final study assessments), the participants will be informed about the deception.

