### Outcomes {12}

Primary outcome measures include:Brain activation in networks implicated in (i) reward and (ii) emotion processing, (iii) placebo and (iv) antidepressant treatment response in MDD and (v) the pathophysiology of MDD (in particular VMPFC, rACC, amygdala, hippocampus).

Secondary outcomes include:Behavioural reaction times and hit rates in the Monetary Incentive Delay task (see Study 2: Reward processing)Expectation-related changes in depressive symptoms (self-rating BDI, expert rating MADRS) in response to placebo and esketamine.

Primary outcomes will be assessed 1 h post treatment, secondary outcomes at 1h, 2h, 4h, 24 h, 3days and 7days post treatment.

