We will analyse task-related fMRI data using the general linear model (GLM) approach. We will investigate the main effects of medication (esketamine vs placebo) and positive expectation (high vs low) using flexible factorial models focusing on predefined regions-of-interest (ROI) including the amygdala, hippocampus, insula, thalamus, ACC/PCC, dorso- and ventrolateral PFC, precuneus, caudate and Nacc (ROIs cf above Functional neuroimaging of emotion and reward processing in MDD). In Study 1 (Emotion processing), we are planning to compare BOLD responses to emotional faces and baseline fixation crosses on a single subject level, using appropriate contrasts that will then be included to a second GLM (group level). In Study 2 (Reward processing), four separate orthogonal regressors will be designed to contrast responses to gain and loss during anticipation and outcome versus neutral conditions (i.e. no-gain and no-loss anticipation and outcome): gain versus no-gain anticipation (GVNant), loss versus no-loss anticipation (LVNant), gain versus no-gain outcome (GVNout), and no-loss versus loss outcome (NVLout) (as used previously; [31]). Generally, based on our hypotheses, a small volume regions of interest (ROI) approach with family wise error correction (FWE) will be applied using predefined anatomical ROIs based on the Harvard Oxford atlas and meta-analyses conducted on the neurosynth.org platform. Relevant variables (e.g. age, gender, treatment expectation scores, type of antidepressant medication other than esketamine [i.e. SSRI, SNRI, other AD, combination pharmacotherapy], severity of depression symptoms) will be included as covariates to control their influence on changes in neural activity in the different experimental phases or to test for their relationship with relevant neural processes (reward processing, emotion processing). Post hoc analyses will explore the effect of type of AD medication. Exploratory analyses will comprise whole brain analyses. In addition to task-related data, functional and structural connectivity will be analysed in order to address the relationship between inter-individual differences in intrinsic functional connectivity and structural connectivity/integrity and expectation-modulation and emotion and reward-processing networks. These analyses will focus particularly on hippocampal-medial prefrontal-amygdala circuits. Morphometric analyses will focus on hippocampus, insula, sgACC and amygdala ROIs and correlate these with treatment outcome. Finally, we will use voxel-based morphometry (VBM) to test for an association between structural predispositions in the abovementioned ROIs and behavioural measures of expectation effects on depression symptoms.

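### Four hypotheses use baseline brain imaging as a predictor, but every scan the text dates comes after induction and dosing; state a pre-dose scan or relabel the predictors

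*Protocol article*

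**What the plan says.** The Hypotheses section of Study 1 contains two predictions from baseline imaging. One concerns task activation: "Baseline activation in regions involved in emotion processing (in particular VMPFC, amygdala) will be predictive of 4-h and 1-week treatment effects". The other concerns connectivity: "Baseline VMPFC and rACC functional (rsfMRI) and structural (DTI) connectivity with amygdala predicts placebo treatment response after 4 h". Study 2 has the matching pair: "Baseline activation in regions of the mesolimbic system during reward processing (in particular hippocampus, NAc) will be predictive of 4-h and 1-week treatment effects" and "Baseline VMPFC and rACC functional (rsfMRI) and structural (DTI) connectivity with hippocampus predicts placebo treatment response after 4 h".

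The scan schedule is given under Factor 2 Expectation (high/low): "One hour after expectation induction and receiving the study medication, patients will undergo MRI measurements: T1, DTI, fMRI resting state and two experimental" paradigms. The Study 1 description has patients perform the face task "after having received the expectation induction followed by the study medication", and the Study 2 description puts the reward task after the same procedure. Outcomes {12} adds: "Primary outcomes will be assessed 1 h post treatment". The baseline assessments listed under Factor 2 are rating scales and questionnaires, with no MRI. The Fig. 1 caption names a baseline assessment on day 0 without describing its content, and mentions scanning only after the sentence on randomisation at day 1.

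**The concern.** A baseline predictor has to be measured before the randomised factors can act on it. On the schedule as written, both factors have acted by the time of the scan. The article's own background reports symptom reduction after ketamine starting within 40 to 60 minutes, and ketamine effects throughout the brain. The second hypothesis of Study 1 expects expectation and medication to move the neural and behavioural measures in the same order of arms. Activation at one hour and symptoms at 4 hours or one week would then share a cause, the arm, and could correlate even if no patient-level prediction exists.

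What is at stake is a report that certain brain measures predict response before treatment, when the stated schedule never measures them then. Under Objectives {7}, the data also go into pooled analyses across the research centre that look for predictors of expectation effects, so a wrong label would travel beyond this trial.

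**Working it through.** **Timing.** Hypotheses that need pre-treatment imaging: 4 (two per study). Scan sessions dated in the text: 1, about one hour after treatment. Pre-treatment scans dated in the text: 0.

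Two further details fit a single session without proving it:
- The group model in Statistical methods {20a} names medication and expectation, but no time or session factor.
- The reward task offers 18 gain trials at each of €0.20, €1.00 and €5.00, so 18 × 6.20 = €111.60 in one 180-trial session. At the intended success rate of about 66%, this is 0.66 × 111.60 = €73.66, in line with the €73.65 maximum payout in section {18b}.

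**Size of the induced correlation, task-activation hypotheses.**

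Inputs:
- Expectation effect d = 0.40, from Sample size {14}.
- Drug effect dm = 0.38 to 1.00, the range for symptom reduction in the esketamine background section.
- n = 4 × 36 = 144 evaluable patients, from Sample size {14}.

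Assumptions, none stated in the article:
- Both effects act equally on activation and on symptom improvement, and add without interaction.
- There is no association within arms, and the within-arm SD is 1.
- The correlation is pooled over the four arms with no arm terms.

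With each factor coded 0/1 in equal proportions, the variance of a factor is 0.25. Hence

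- covariance c = 0.25 × (0.40² + dm²)
- variance of each measure = 1 + c
- r = c / (1 + c)

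Rejection rate by Fisher z: shift = atanh(r) × √(144 − 3), compared with ±1.96.

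| dm | c | r | shift | rejection at nominal 5% |
|---|---|---|---|---|
| 0.38 | 0.076 | 0.071 | 0.84 | 13% |
| 0.70 | 0.163 | 0.140 | 1.67 | 39% |
| 1.00 | 0.290 | 0.225 | 2.72 | 78% |

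Simulation with 36 patients per arm gives 13%, 40% and 79%. With medication, expectation and their product in the model, the rate returns to about 5% (4.4% to 5.4%).

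**Placebo-response connectivity hypotheses.** Only the two placebo arms enter, n = 2 × 36 = 72, and only expectation differs between them.

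- c = 0.25 × 0.40² = 0.04
- r = 0.04 / 1.04 = 0.038
- shift = 0.0385 × √69 = 0.32
- rejection about 6%, close to nominal

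Here arm confounding is negligible on these assumptions. What remains is that a resting-state scan taken after the induction is not a baseline measure.

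**The case against.** The strongest reply is that the article refers the sequence of data collection to Table 1 and Fig. 1, and neither could be seen. The day-0 baseline visit might include a scan. This stands, and it makes the consequence conditional. A reader might infer that the trial certainly never measured a baseline brain state; the visible text does not establish that. Nor would a pre-dose scan contradict the schedule text. The Factor 2 section describes the post-dose session without calling it the only one, and Outcomes {12} dates outcomes, not predictors. Those sections would be incomplete.

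A reader might also take the aim "to control their influence on changes in neural activity in the different experimental phases" in section {20a} as a second sign of a missing scan, on the ground that change needs two scans. That does not follow. Task activation is itself a contrast within one session (faces against fixation, gain or loss against neutral), and the phases can be the phases of the task.

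The 13% to 78% range depends on an unadjusted pooled correlation, and the article specifies no model for these hypotheses; a fuller plan may include arm terms. It also carries symptom effect sizes over to activation, which the documents do not support beyond the ordering they hypothesise. The range therefore shows what could happen under one analysis. It is not an error rate of the plan.

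Structural connectivity from DTI is an anatomical measure and may well be stable over an hour, so it should not be grouped with the brain responses. Finally, the one-hour scan still precedes the 4-hour and one-week outcomes, so it keeps its value as an early marker.

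**Conclusion.** The point holds as a conflict between four hypotheses and the scan times in the text. If no pre-dose scan exists, task activation and resting-state connectivity are measured after treatment and cannot support pre-treatment prediction. For task activation, leaving out arm terms could also produce spurious association: r of 0.07 to 0.22, with rejection in 13% to 78% of trials, under the assumptions listed. For the placebo-response hypotheses the induced r is about 0.04 with about 6% rejection, so the fault is mainly the label. DTI is least affected.

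It would be wrong to infer that the trial's main results are compromised. The randomised comparisons of activation at one hour and of symptoms do not use these predictors. The trial is declared exploratory, and the four hypotheses lie outside the listed primary and secondary outcomes. The point should be corrected before analysis, but it does not rank with errors that threaten the primary result.

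**What to change.** **If a pre-dose scan exists:** state it in the Factor 2 section, where the MRI session is described, and use that scan as the predictor.

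**If none exists:**
- In both Hypotheses sections, replace the word baseline, for task activation and resting-state connectivity, by a description such as 1-h post-induction, post-dose. Call these measures early post-treatment markers.
- In the task-activation models, regress the 4-hour and one-week scores on the regional measure with medication, expectation and their product included. In the placebo-only models, include the expectation term.
- Report within-arm slopes and make no claim of pre-treatment prediction.
- Keep DTI as a trait measure only under the stated assumption that it does not change within the hour.

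In either case the wording of section {20a} on changes in neural activity can stay. The cost is revised wording and a few model terms, with no extra scan or patient. The price is a weaker claim: an early marker of response in place of a baseline predictor.
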